## Statistical methods

Data will be analysed according to the modified intention-to-treat principle (i.e., all patients with a 3-month evaluation will be analysed as randomised). The intention-to-treat principle will be applied from the time that patients have initiated treatment (i.e., after the brief interview protocol that includes elements from the SCAN interview and motivational interviewing). Categorical variables will be summarised as n (%), continuous variables as min-max, mean (SD), and median. All summaries will be by randomisation group. The primary analysis will be a linear regression of depression scores at 3 months including randomisation group and strata as factors and baseline depression scores as covariate. Potential confounders, apart from baseline and stratification variables, identified by clinical consensus, will be included in multivariable analyses when appropriate (e.g. when performing sub-group analyses). A mixed effects model will be used to analyse the longitudinal change in HADS scores and HeartQoL scores, adjusting for strata, incorporating random effects to model the homogeneity within cluster and the correlation within patient across time. Pre-planned subgroup analyses will be conducted for the primary outcome with respect to: *(i)* type of IHD (stable versus unstable); *(ii)* sex (female versus male); *(iii)* age (median split); *(iv)* depression status at baseline (< 10 versus ≥11; *≥11 is considered a moderate score*). A sensitivity analysis will be conducted. The statistical analysis will be transparent, subject to review and approval by the project team.

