## Sample size calculation

Based on Stauber et al. [34], a conservative estimate of the standard deviation of the mean of the HADS depression score at 3 months is 3.5. The minimal clinically important difference for the HADS is 2 points [35]. For a normal-based comparison of independent means, with a power of 90% (ß = 0.1) and a risk of Type 1 error of 5% (α = 0.05), the estimated required number of patients is *n* = 66 in each group. Considering a potential 30% dropout rate, the estimated number of needed participants is *n* = 94 patients in each group (n (total) = 188).

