## Randomisation, blinding and treatment allocation

Patients will be randomised 1:1 to **(i)** TAU + *eMindYourHeart* intervention to treat psychological comorbidity versus **(ii)** TAU alone. The randomisation will be stratified by site and stable versus unstable IHD. Randomisation will be performed in the internationally recognised data capture platform – Research Electronic Data Capture (RedCap) – by an independent researcher who will be blinded to the allocation list. Patients and therapists will be informed of treatment allocation after randomisation is final. A merged blocks permutation stratified by inclusion centre will be used. This adaptation of a stratified block randomisation is better suited to small clinical trials where regular block randomisation would compromise predictability [39]. The randomisation list will be created using the mergedblocksmulti function of the mergedblocks package in R3.6.0 for Windows [40] and will only be accessible to the researcher who created the list (RK). Apart from the psychologists delivering the therapy, the research team will be blinded to treatment allocation. Due to the nature of the intervention, it is not possible to blind patients to their trial condition.

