## Other measures

Information on patients’ demographic and clinical characteristics at baseline will be captured from patients’ medical records at the rehabilitation centre *or* the hospital, DHRD*, or* via purpose-designed questions. These questions will be included in the questionnaire sent to patients at baseline with standardised and validated measures (Table 3).

Measures of total health care costs measured in EUR will be collected from the Danish administrative health care registers. Loss of labour market productivity will be calculated using the human capital approach where average wages are used to estimate loss of work productivity. Costs will be measured in 2020 prices using a currency rate of 1 EURO to 7.45 DKK. Health care costs include all hospital utilisation aggregated using the Danish diagnosis-related group (DRG) prices (somatic and psychiatric care). Primary care services will be aggregated using national health insurance service fees (including GPs and private practicing specialists). Total utilisation of prescription drugs will be measured by purchasing prices of the patient excluding value added tax (VAT).

Cost-utility will be measured by estimation of the incremental costs for a gain in QoL. Costs will be covering intervention costs and 12-month total health care utilisation. Thus, the cost-utility analysis will be carried out using the perspective of the health care sector. QoL will be measured using HeartQoL at 3, 6 and 12 months. A probabilistic approach will be used to assess uncertainty and acceptability curves will estimated.

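### The only stated analysis set requires a 3-month evaluation and does not exempt the economic analysis, so as written it drops 12-month costs that would still be available from registers

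*Protocol article*

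**What the plan says.** The Statistical methods section of the protocol article opens with the analysis population: "Data will be analysed according to the modified intention-to-treat principle (i.e., all patients with a 3-month evaluation will be analysed as randomised". The rule is stated for data in general. The next sentence starts the intention-to-treat principle only once treatment has begun. Neither sentence mentions the economic outcome, and no other analysis set appears in the article.

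The cost-utility analysis is described under Other measures. On the cost side: "Measures of total health care costs measured in EUR will be collected from the Danish administrative health care registers", and "Costs will be covering intervention costs and 12-month total health care utilisation". On the effect side it uses HeartQoL at 3, 6 and 12 months. Table 3 lists HeartQoL and EQ-5D-5L at baseline, end of treatment, 6 and 12 months. The section promises a probabilistic analysis and acceptability curves but does not say which patients enter them.

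Three other statements bear on the point:
- The sample size section inflates the target for loss: "Considering a potential 30% dropout rate, the estimated number of needed participants" is 94 per group.
- Ethics and safety considerations says that patients who drop out are followed up under intention-to-treat, whereas withdrawn subjects are not followed up.
- The section defining adherence and dropout counts as a dropout only a patient who tells the therapist that they wish to stop. Silent non-responders stay enrolled.

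**The concern.** A 3-month evaluation is a natural entry condition for a regression of 3-month depression scores. It is a poor one for 12-month costs. Register costs exist whether or not the patient answers at 3 months, and intervention spending on a patient who later falls silent has still been incurred. Someone who misses month 3 may also return HeartQoL at 6 or 12 months.

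Two things are at stake. First, precision is lost on a quantity that could be observed for nearly everyone. Second, entry to the cost comparison depends on an event after randomisation, in a trial where patients know their allocation. If those who miss the evaluation differ in cost from those who attend, and the difference or the rate of missing is not the same in both arms, the incremental cost is no longer protected by randomisation. Cost-effectiveness is part of the trial's stated aim, so this is not a marginal outcome.

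**Working it through.** **1. The plan's own figure.** Inputs from Sample size calculation: SD 3.5, difference 2 points, "with a power of 90% (ß = 0.1) and a risk of Type 1 error of 5% (α = 0.05". The test is taken as two-sided, since a one-sided test gives 53 per group and does not reproduce the stated number. Allocation is 1:1.
- Normal approximation: n = 2 × [3.5 × (1.960 + 1.282) / 2]² = 64.4, so 65 per group.
- Two-sample t-test: 65.3, so 66 per group, as stated.
- Inflation for 30% loss: 66 / 0.70 = 94.3, stated as 94, and 2 × 94 = 188.

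The sample size reproduces.

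**2. Patients outside the analysis set.** The 3-month missing rate is not given. The 30% allowance serves as a planning upper figure, with 10% and 20% as assumptions.
- All 30% missing: 2 × 66 = 132 kept, 188 − 132 = 56 left out (56 / 188 = 29.8%).
- 20% missing: 188 × 0.20 = 37.6, about 38 left out.
- 10% missing: 188 × 0.10 = 18.8, about 19 left out.

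**3. Precision of the cost difference.** With the same cost SD and equal loss per arm, SE = SD × √(2/n), so the ratio of the restricted to the full SE is 1/√(1 − m), where m is the missing share.
- m = 0.30: 1/√0.70 = 1.20.
- m = 0.20: 1/√0.80 = 1.12.
- m = 0.10: 1/√0.90 = 1.05.

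**4. Bias.** In each arm, let g be the mean cost of patients missing the evaluation minus that of patients attending it. The mean over the full arm equals the attenders' mean plus m × g. The true cost difference (intervention minus usual care) therefore exceeds the attenders' difference by

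m(intervention) × g(intervention) − m(usual care) × g(usual care).

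This is zero when m and g are the same in both arms, and generally not otherwise. The article gives no cost mean or SD, no missing rate by arm and no value for g, so no figure can be put on it.

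**5. The sections side by side.** Ethics and safety considerations has dropouts followed up under intention-to-treat. Statistical methods then admits only those with a 3-month evaluation. A patient followed to 12 months but missing month 3 is thus collected and then left out.

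**The case against.** The strongest reply is that the cost-utility analysis is described in its own section and the analysis-set sentence may never have been meant to govern it. An article also commonly leaves missing-data handling for an economic analysis to the full protocol or the analysis plan. The second part stands: the absence of an imputation method is no fault here. The first part does not settle the matter, because the article states one population without exception and names no other.

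A reader might also infer more than the article supports:
- **That patients without a 3-month questionnaire cannot be scored for cost-utility.** HeartQoL is also collected at baseline, 6 and 12 months, and a mixed model that can use incomplete series is planned for it. The exclusion comes from the set rule.
- **That 30% are planned to lack the 3-month evaluation.** The figure is a potential dropout rate. Dropout means actively stopping treatment, and dropouts are still followed up. The share missing at month 3 is not tied to it.
- **That the result would describe questionnaire completers only.** The rule requires month 3 alone, not months 6 and 12.
- **That the bias can be sized from the 33% extra cost of depression in the Background.** That figure compares patients with and without depression. It says nothing about non-responders against responders in a trial where everyone screens positive for depression, anxiety or both.

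**Conclusion.** The point holds as a fault in a stated rule. Followed as written, the plan leaves out available register and intervention costs, and any later HeartQoL scores, for patients without a 3-month evaluation. It also makes the cost comparison depend on a post-randomisation event.

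The loss is up to about 56 of 188 patients, with a standard error about 1.2 times larger, if the whole dropout allowance turns into missing 3-month evaluations. It is smaller at lower rates. These figures assume equal loss in both arms and an unchanged cost SD. Bias is possible, but its size and direction cannot be computed from the article, and it could be nil. The sample size is not in question, and the point does not touch the primary outcome. The change is worth making because a headline secondary result is exposed at little cost to repair.

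**What to change.** State in Other measures and in Statistical methods that the cost-utility analysis includes all randomised patients, as randomised. Word the sentence that starts intention-to-treat at treatment initiation so that it does not bring a restriction back in.

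Use 12-month register costs and intervention costs for each patient whose register data may be used. Reconcile this with the statement in Ethics and safety considerations that withdrawn subjects are not followed up, so that it is clear whether their register data may be used.

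Handle missing HeartQoL by a method valid under missing at random, either a mixed model or multiple imputation, so that costs and QoL refer to the same population. The choice between them can be left to the analysis plan. Keep the 3-month-evaluation set as a sensitivity analysis.

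The cost is a few sentences and modest programming in the probabilistic step. No new data source is needed. The small downside is that the QoL side then relies on a missing-at-random assumption.

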#### Secondary objectives

The secondary objectives are to evaluate the efficacy of the eHealth intervention targeting depression and anxiety + TAU as compared to TAU alone on symptoms of anxiety, perceived stress, health complaints, QoL, and dropout (number of patients dropped out in either arms at 3 months) at 3 months, and symptoms of depression, anxiety, perceived stress, health complaints, and QoL at 6 and 12 months’ follow-up and cost-effectiveness/cost-utility.

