#### Hypotheses

Given the user-centered, therapist-assisted eHealth approach to treat depression and anxiety, allowing patients to engage in the intervention when and where they want, we hypothesise that the intervention will be broadly acceptable to patients, have a low dropout rate and be effective and cost-effective.

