## Trial outcomes

Primary: Symptoms of depression, measured with HADS at the end of the intervention (i.e., 3 months).

Secondary: Symptoms of anxiety measured with HADS at 3 months; symptoms of depression and anxiety at 6- and 12 months’ follow-up; QoL (HeartQoL) at 3, 6, and 12 months follow-up; trial dropout (number of patients dropped out in either arms at 3 months) and cost-effectiveness/cost-utility.

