## Definition of treatment adherence and dropout

In internet-based therapy, research it is often unclear how treatment adherence is defined and there seems to be no gold standard [42]. However, use of different definitions across studies makes comparisons difficult with respect to efficacy of internet-based therapy. In *eMindYourHeart*, we define treatment adherence by the number of modules that the patient completes. Since treatment needs of individual patients may vary and we have elective modules that will be allocated to patients based on their needs, a module is considered completed, when the therapist judges that the individual patient has worked sufficiently with the exercises in the module. For example, if a patient primarily suffers from depression and not anxiety, the module focusing on exposure therapy is likely not relevant. The therapist’s judgement is made according to guidelines specified in the treatment manual. This ensures consistency across therapists and enhances the fidelity of the study.

A patient is considered a dropout, if the patient actively informs the therapist that the patient wishes to stop treatment. A patient who, at some point during treatment, stops adhering to treatment and does not respond to the therapist, will not be considered a dropout, but will stay enrolled in the treatment until the end of the 12-week treatment duration.

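### The only stated analysis set requires a 3-month evaluation and makes no exception for trial dropout at 3 months, so dropouts without that evaluation go uncounted

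*Protocol article*

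**What the plan says.** The protocol article's Statistical methods section opens with a rule for the data as a whole. It calls the rule modified intention-to-treat and explains it as "all patients with a 3-month evaluation will be analysed as randomised". The next sentence narrows the population from another side: "The intention-to-treat principle will be applied from the time that patients have initiated treatment". Neither sentence names an outcome to which it does not apply.

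Dropout is one of the outcomes. The Abstract lists it, Secondary objectives include "dropout (number of patients dropped out in either arms at 3 months) at 3 months" among the comparisons of the two arms, and Trial outcomes lists "trial dropout (number of patients dropped out in either arms at 3 months" as secondary. Under Hypotheses, the intervention is expected to "have a low dropout rate and be effective and cost-effective".

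Three other places bear on how many dropouts will have a 3-month evaluation:

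- Definition of treatment adherence and dropout: "A patient is considered a dropout, if the patient actively informs the therapist that the patient wishes to stop treatment". A patient who stops adhering and does not answer the therapist "will not be considered a dropout, but will stay enrolled in the treatment until the end of the 12-week treatment duration".
- Ethics and safety considerations: patients who drop out are to be followed up on intention-to-treat lines, whereas patients whom the investigator withdraws are not followed up.
- Sample size calculation: "Considering a potential 30% dropout rate, the estimated number of needed participants" is raised from 66 to 94 per arm.

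**The concern.** The analysis set is defined by being observed at 3 months. The outcome is about leaving by 3 months. The two are not the same thing, but they are closely linked, and the link makes this set a poor denominator for dropout. A dropout with no 3-month evaluation is removed before the arms are compared. A silent patient with no evaluation is removed as well, although that patient counts as retained under the article's own definition. The reported rates then depend on who returned a questionnaire as well as on who dropped out.

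At stake is a listed secondary outcome and one of the stated hypotheses. Dropout by arm is also what a reader would use to judge attrition bias in a primary analysis that is itself limited to patients with a 3-month evaluation.

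**Working it through.** **1. The plan's own figure.** Inputs from Sample size calculation: SD 3.5, difference 2 points, power 90%, type 1 error 5% (taken as two-sided, which the article does not state).

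- Normal approximation: n = 2 × (1.960 + 1.282)² × 3.5² / 2² = 64.4, so 65 per arm. The t-test version gives 65.3, so 66, as stated.
- Inflation: 66 / (1 − 0.30) = 94.3, stated as 94 per arm and 188 in total. In reverse, 94 × 0.70 = 65.8.

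The figure reproduces. The inflation treats every one of the 30% as giving no usable 3-month score.

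**2. The analysed dropout rate under the stated set.** Let d be the true dropout proportion, f the share of dropouts with a 3-month evaluation, and g the share of non-dropouts with one. Then

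analysed rate = d·f / [d·f + (1 − d)·g].

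The article gives neither f nor g, so both are varied. As an illustration take d = 0.30, although that figure is an allowance for missing scores and not a forecast of the defined dropout event. With 188 randomised this is 56.4 dropouts and 131.6 others. With g = 1:

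| f (assumed) | Dropouts removed | Analysed rate |
|---|---|---|
| 0 | 56.4 | 0 / 131.6 = 0% |
| 0.25 | 42.3 | 14.1 / 145.7 = 9.7% |
| 0.50 | 28.2 | 28.2 / 159.8 = 17.6% |
| 0.75 | 14.1 | 42.3 / 173.9 = 24.3% |
| 1 | 0 | 56.4 / 188 = 30% |

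The first row is what the sample-size inflation implies. The last row is what full follow-up of dropouts, as promised under Ethics and safety considerations, would give.

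**3. Direction.** The table assumes that every non-dropout is evaluated. Silent patients are not dropouts, so g may well be below 1.

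- If f = g, the formula returns d and the rate is unbiased.
- If f is larger than g, the rate is too high. With f = 0.75 and g = 0.50 (both assumed): 0.225 / (0.225 + 0.350) = 39.1%.

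**4. Between the arms.** The set can also create a difference. Take 30% true dropout in both arms and g = 1, with an assumed f of 0.25 in one arm and 0.75 in the other. The analysed rates are 9.7% and 24.3%, a gap of 14.6 points where none exists.

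**The case against.** The strongest reply is that the analysis set is not the complement of the event. By definition a dropout is a patient who tells the therapist of a wish to stop treatment, and the article says dropouts will be followed up. Such a patient can still complete the 3-month questionnaire and stay in the set. This stands. A reader might infer that most dropouts are removed, or that a low dropout rate is guaranteed by construction. The article supports neither. With complete evaluation of non-dropouts, most are lost only if fewer than half of the dropouts are evaluated, and nothing in the text says so. Silent patients leaving the denominator could even push the rate upwards.

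The reply also notes that the 30% is an allowance for missing scores, so 56 of 188 is not a prediction of dropout events. That stands too, and the figures above are illustrations only. The article states no expected difference in dropout between the arms, so no power figure for that comparison can be drawn from it.

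A third argument is that the section goes on to name models only for HADS and HeartQoL scores, and that the denominator for one secondary outcome can be left to the analysis plan. This carries less weight. The article does not leave the matter open: it fixes a set, applies it to the data without exception, and lists an outcome for which that set is unsuitable. An analysis plan that followed the article would inherit the problem.

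**Conclusion.** The point holds in limited form. As written, any dropout without a 3-month evaluation is excluded before dropout is compared, and silent non-responders may be excluded from the denominator. The rates and their difference can be distorted. Neither the size nor the direction is known from the document. On the illustrative 30%, with all non-dropouts evaluated, the analysed rate lies anywhere from 0% to 30%, depending on an unstated share of evaluated dropouts. With incomplete evaluation of non-dropouts it can exceed the true rate.

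The conclusion rests on reading the opening rule of Statistical methods as covering every outcome, which is its plain wording. It concerns a secondary outcome. The primary analysis and the sample size do not change.

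**What to change.** In Statistical methods, or in the analysis plan before any unblinded analysis:

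- Limit the requirement of a 3-month evaluation to the questionnaire scores.
- State that trial dropout at 3 months is analysed in all randomised patients by allocated arm, as a difference in proportions with a 95% confidence interval that accounts for the randomisation strata.
- Reconcile this with the sections on dropout definition and on ethics and safety. The definition is worded around telling a therapist of a wish to stop treatment, which has no evident counterpart for a patient on treatment as usual alone. The same event has to be counted in both arms, or the larger denominator will not make the comparison fair.

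The change of denominator takes one sentence. Aligning the definition takes more thought, because the article does not show that dropout status is recorded in a comparable way in the usual-care arm. The other cost is that the reported dropout rate may look less favourable.

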## Ethics and safety considerations

Ethical approval for the trial is obtained from the Regional Committees on Health Research Ethics for Southern Denmark [S-20180024] (version 5 approved 10 September 2019). The required permissions are obtained from the Danish Data Protection Agency via Odense University Hospital (17/41433 on November 24, 2017). The trial will be conducted according to the Helsinki Declaration and was prospectively registered on http://www.clinicaltrials.gov [NCT04172974]. All patients will receive oral and written information about the trial and sign an informed consent form. Patients who do not wish to participate in the trial are asked about *(i)* the reason and *(ii)* whether we may use the patient’s data from the rehabilitation setting and the Danish Cardiac Rehabilitation Database (DHRD). DHRD is a Danish quality database that collates health data on CR from all hospitals in Denmark to ensure cohesiveness and quality in CR in Denmark [36]. It is compulsory for all hospitals offering CR to report into the database.

Subjects can leave the trial at any time for any reason if they wish without any consequences. The investigator can decide to withdraw a subject from the trial due to urgent medical reasons. Subjects withdrawn from the trial will not be replaced and will not be followed-up. Subjects who drop out of the trial will be followed up according to the intention-to-treat principle [37].

There are no expected medical risks associated with trial participation, as medical treatment is provided according to national clinical guidelines [14] and the trial compares two types of care (i.e., *(i)* TAU + eHealth intervention versus *(ii)* TAU. However, we cannot rule out that the eHealth intervention may induce additional depression and anxiety in some patients [38]. The Ethics Committee does not require us to have a Data Safety Monitoring Board (DSMB), but annually we are required to report serious side effects and incidents to the Committee.

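### The rule that only patients with a 3-month evaluation are analysed also governs the mixed model, so it excludes patients who miss month 3 but answer at 6 or 12 months

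*Protocol article*

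**What the plan says.** All of this is in the protocol article.

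- **Analysis set (Statistical methods).** The section opens with a modified intention-to-treat rule for the data as a whole: "all patients with a 3-month evaluation will be analysed as randomised". The next sentence starts intention-to-treat from the initiation of treatment. It does not lift the month-3 condition.
- **Longitudinal model (same section).** "A mixed effects model will be used to analyse the longitudinal change in HADS scores and HeartQoL scores", adjusted for strata and with random effects. No separate analysis set is given for it.
- **Long-term outcomes.** Secondary objectives lists "symptoms of depression, anxiety, perceived stress, health complaints, and QoL at 6 and 12 months". Trial outcomes lists "symptoms of depression and anxiety at 6- and 12 months" and "QoL (HeartQoL) at 3, 6, and 12 months follow-up". Table 3 schedules HADS and HeartQoL at both later visits.
- **Follow-up (Ethics and safety considerations).** "Subjects who drop out of the trial will be followed up according to the intention-to-treat principle". Patients withdrawn by the investigator for urgent medical reasons are not followed further.
- **Silent patients (Definition of treatment adherence and dropout).** A patient who stops engaging and does not reply to the therapist "will not be considered a dropout, but will stay enrolled in the treatment until the end of the 12-week treatment duration".

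**The concern.** Requiring a month-3 evaluation follows naturally for a regression of the month-3 score. For an outcome measured at 6 or 12 months it serves no purpose: a patient with baseline, month-6 and month-12 scores has the data the comparison needs and is still excluded.

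Two things are at stake.

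- **Precision.** Data that the trial plans to collect would not be used.
- **Validity.** A likelihood-based mixed model handles a missed visit under a missing-at-random assumption by using all the data that each patient supplies. Selecting beforehand on a response made after randomisation gives up that advantage. Month-3 response could plausibly differ by arm, because patients know their allocation and only the intervention arm has scheduled therapist calls and messages.

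The point concerns the secondary 6- and 12-month comparisons. It does not touch the primary month-3 regression or the sample size.

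**Working it through.** **1. The plan's own figure.** Inputs from Sample size calculation: difference 2 points, SD 3.5, power 90%, alpha 5% (taken as two-sided), dropout 30%.

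- Normal approximation: n = 2 × (1.960 + 1.282)² × 3.5² / 2² = 64.4, so 65 per arm.
- The two-sample t version gives 66 (power 90.3%; 65 gives 89.9%), which matches the article.
- 66 / 0.7 = 94.3, stated as 94 per arm and 188 in total.

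The sample size reproduces. It rests on patients evaluable at month 3, so it is unaffected here.

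**2. How many patients the rule could reach.** If the whole 30% allowance is missing at month 3, that is 94 × 0.30 = 28.2 per arm, about 56 in total. Let f be the share of these who answer at month 12, and r the share of month-3 completers who do. The article gives neither, so both are assumptions.

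**3. Precision at month 12.** This is a simple cross-sectional approximation with SD 3.5.

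- Kept under the rule, per arm: 94 × 0.70 × r
- All available, per arm: 94 × 0.70 × r + 94 × 0.30 × f
- SE = 3.5 × √(2 / n per arm)

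| r | f | n, rule | n, all | SE, rule | SE, all | SE larger by |
|---|---|---|---|---|---|---|
| 100% | 0% | 65.8 | 65.8 | 0.610 | 0.610 | 0% |
| 100% | 10% | 65.8 | 68.6 | 0.610 | 0.598 | 2.1% |
| 100% | 25% | 65.8 | 72.8 | 0.610 | 0.580 | 5.2% |
| 100% | 50% | 65.8 | 79.9 | 0.610 | 0.554 | 10.2% |
| 80% | 10% | 52.6 | 55.5 | 0.682 | 0.665 | 2.6% |
| 80% | 25% | 52.6 | 59.7 | 0.682 | 0.641 | 6.5% |
| 80% | 50% | 52.6 | 66.7 | 0.682 | 0.606 | 12.6% |

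For a 2-point difference at month 12 with f = 50%, power is 90.6% under the rule against 95.1% with all data when r = 100%, and 83.4% against 91.0% when r = 80%. A mixed model that also uses the other visits may give somewhat different figures.

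**4. Bias when month-3 response depends only on baseline, differently by arm.** Large-sample simulation: SD 3.5, correlation 0.5, 27% to 30% missing month 3, true effect −1.5.

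- Higher baseline raises non-response in the intervention arm only: the unadjusted change from baseline among month-3 responders gives −1.06.
- The pattern reversed: −1.94.
- The same responders with the 12-month score adjusted for baseline: about −1.50 both ways, so no bias.

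Under this mechanism the bias depends on how baseline enters the model, and its sign depends on the assumed pattern.

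**5. Bias when month-3 response is related to the later outcome.** Large-sample simulation: month-3 non-response in the intervention arm is more likely with a worse 12-month score and is random in the control arm; about 30% missing per arm; true effect −2.0; baseline adjusted.

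| Analysis | Estimate | Error |
|---|---|---|
| Month-3 evaluation required | −2.62 | −0.62 |
| Later responders included, f = 25% | −2.42 | −0.42 |
| Later responders included, f = 50% | −2.25 | −0.25 |
| Later responders included, f = 100% | −2.01 | −0.01 |

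Including later responders leaves 0.42 / 0.62 = 68% of the error at f = 25% and 0.25 / 0.62 = 40% at f = 50%. If the same selection acted in the control arm instead, the error would change sign by symmetry (−2.0 + 0.62 = −1.38). If month-3 response is unrelated to outcome, only precision is lost.

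**The case against.** **The sentence may be shorthand.** The primary outcome is at month 3, the rule is a parenthesis in a condensed article, and the authors may have meant it for the primary analysis only. That is possible. But the rule is stated for the data in general, the mixed model follows under it, and no other set appears. This is a rule that is written down, not a detail left to an analysis plan. A sensitivity analysis is announced but not described, so it does not settle the matter.

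**A reader might infer that the rule contradicts the follow-up of dropouts.** The article does not support that. One passage concerns who is followed and the other who is analysed. Dropout is defined as telling the therapist that one wishes to stop treatment, not as missing a questionnaire. A treatment dropout who answers at month 3 is both followed and analysed. What remains is a tension: later data may be collected under an intention-to-treat heading and then not used.

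**A reader might also infer a large bias of known direction, or that randomisation protects nothing once the rule is applied.** Neither follows. The shrinkage in step 4 of the working appears only in an unadjusted change-from-baseline contrast. The article names baseline as a covariate for the primary regression but does not say how it enters the mixed model, which is a detail an article may leave out. Non-response at month 12 would also weaken the comparison whatever the analysis set.

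**The cost may be small.** This stands. If nobody returns after missing month 3, precision in this approximation is unchanged, and the outcomes are secondary.

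**Conclusion.** The concern holds as a limited point. As written, the month-3 requirement reaches the mixed model and excludes usable 6- and 12-month HADS and HeartQoL data.

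The avoidable precision loss is roughly 0% to 13% in the 12-month standard error. That range assumes 30% missing at month 3, a return rate of 0% to 50%, and 80% to 100% of month-3 completers answering at month 12.

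Bias in either direction is possible when month-3 response is related to arm and later outcome. Its size cannot be fixed from the article, and the simulated values only illustrate it. Using all available data reduces this bias but may not remove it. The change is worth making because it is specific and nearly free.

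**What to change.** - Limit the 3-month-evaluation requirement to the primary month-3 regression.
- For the mixed model of HADS-D, HADS-A and HeartQoL, include every randomised patient with any available assessment, baseline included, analysed as randomised.
- Keep the set of patients with a month-3 evaluation as a sensitivity analysis for the 6- and 12-month contrasts.
- When making the change, state how baseline enters the mixed model, since step 4 of the working shows that this matters.

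The cost is a sentence or two in the statistical methods, with no new data and no extra patients. The article reports 31 of 188 patients included at the time of writing, so at that stage the change could be made well before results were known.
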